### Ethical Requirements and Registration

This study protocol was approved by the Ethics Committee of the Guangzhou University of TCM (Guangzhou, China) in July 2019 and was designated with permission number K2019-007. The trial was registered in the Chinese Clinical Trial Registry with approval number ChiCTR2000030871.

### Blinding

All evaluations were blinded. The person in charge of the efficacy evaluation was hired separately and was not aware of the grouping situation of the patients. The person in charge of the data analysis was also hired separately and did not participate in the subjects' specific clinical implementation work and/or design scheme.

### Interventions

To ensure the participants' safety and compliance and fulfill ethics necessities, we followed the recommendation of the Chinese Guidelines for the management of patients with PD (14). All participants in two groups received Madopar, whose dosage was recorded in detail. The original drug solutions and dosage were changed if the patients had already taken the anti-Parkinson's medicine before recruitment. In some cases, if the medications needed to be altered, the details were recorded carefully, such as the drug's name, administration time, and dosage. The whole treatment was carried out by licensed acupuncturists who had more than 5 years of clinical experience.

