### Inclusion Criteria

The inclusion criteria in this study are as follows: (1) patients with PD, (2) patients of the age of 40–80 years old, (3) patients with a duration of PD of more than 1 year; (4) modified Hoehn-Yahr (HY) grades from 1 to 4; (5) patients who needed to take a stable dose of anti-PD drugs for more than 2 months, if treated with anti-PD drugs, or patients who had not received anti-PD medication for more than 2 months; (6) had clear consciousness and stable vital signs; and (7) patients who fully understood the study protocol and signed the consent form.

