### Sample-Size Calculation

This trial used a clinical-superiority design to verify that QHN therapy's effect was superior to that of sham acupuncture. The primary outcome measure was the UPDRS-III score difference before and after the treatment. According to previous research (17), assuming the standard deviation (SD) to be 8.0 and the mean of the treatment effect of the two groups to be 4.36 and 0.25, respectively, the statistical power was 80%, and the significance level was 0.05. Using PASS software requires each group to contain no <61 patients. With an estimated 15% dropout rate, we planned to recruit 72 patients for each group, for a total of 144 patients.

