### Safety and Adverse Events (AEs)

Acupuncture is generally regarded as a safe therapy. Although AEs of acupuncture are rare, participants still may encounter hematoncus, dizziness, or fainting. If the above events occur, the acupuncture treatment will be stopped immediately, and the subject will be instructed to lie flat on the bed and drink warm water. AEs are caused by oral drugs that mainly include nausea, vomiting, dyspepsia, abdominal distension, orthostatic hypotension, hypohepatia, and renal function impairment. If these adverse reactions occur, participants will halt the use of medication, the respective alternative medicine, and symptomatic treatment as necessary. These AEs will be subcategorized by severity: mild, moderate, and severe AEs. For this study, mild AEs were defined as transient and tolerable AEs. Moderate AEs were defined as those that caused discomfort and potentially interfered with the subject's daily life. Severe AEs were defined as those that seriously affected the participants' physical health and even led to the risk of life. The details of AEs, such as time, duration, performance, measures to be taken, and the outcome, were recorded. The trial was stopped if there was an unacceptable risk of serious AEs in one or both treatment arms.

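### Inclusion criteria and Interventions contradict each other on background anti-PD medication, so the UPDRS-III change may include a drug effect that is common to both arms but not controlled

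*Protocol article*

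**What the plan says.** All references are to the protocol article.

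- **Inclusion Criteria, item 5**, admits two kinds of patient. The first kind is on treatment: "patients who needed to take a stable dose of anti-PD drugs for more than 2 months, if treated with anti-PD drugs". The second kind is off treatment at entry: "patients who had not received anti-PD medication for more than 2 months".
- **Interventions** sets the drug background during the trial: "All participants in two groups received Madopar, whose dosage was recorded in detail". For those on anti-PD drugs at recruitment it states: "The original drug solutions and dosage were changed if the patients had already taken" (the sentence ends by naming such drugs). The sentence after that reads: "In some cases, if the medications needed to be altered, the details were recorded carefully".
- **Safety and Adverse Events** adds that after a drug reaction "participants will halt the use of medication", with alternative medicine and symptomatic treatment as needed.
- **Outcome Measurements** takes baseline before treatment. The Abstract defines the primary outcome as UPDRS-III change from baseline to weeks 6 and 14.
- **Statistical Analysis** compares the groups by t-test or a rank test and names no covariate.

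**The concern.** Item 5 looks designed to give each patient a steady drug background at entry. That purpose is inferred, but it is hard to see another. Interventions, as printed, ends that steadiness for everyone: off-drug patients start Madopar, and treated patients have their drugs and doses changed. A site cannot tell from the text whether it should change a stable regimen or leave it alone.

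This reaches the primary endpoint because UPDRS-III is a motor score, and the article's Background calls dopamine substitution the foundation of PD drug therapy. If drugs are started or changed between baseline and week 6 or 14, the change score contains both a drug component and a needling component. At stake are the meaning of the change within each arm, the precision of the comparison and, under a further condition, its validity.

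**Working it through.** **1. The plan's own figure.** The planned difference is 4.36 − 0.25 = 4.11 points with SD 8.0, 80% power and alpha 0.05 (Sample-Size Calculation). The normal approximation, two-sided, gives n = 2(1.960 + 0.842)² × 8.0² / 4.11² = 59.5, so 60. The t-test version gives 60.45, so 61 per group. With 15% dropout, 61 / 0.85 = 71.8, so 72. The stated 61 and 72 reproduce, and this point does not dispute them.

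**2. The medication statements side by side.**

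| Patient at entry | Item 5 requires | Interventions as printed | Interventions if *unchanged* was meant |
|---|---|---|---|
| Stable on Madopar | Stable dose, more than 2 months | Drugs and dose changed: stability ends | Consistent |
| Stable on another drug | Stable dose, more than 2 months | Regimen changed, Madopar given | Madopar given, yet regimen unchanged: conflict |
| Off anti-PD drugs | No drug, more than 2 months | Madopar started: off-drug state ends | Madopar still started: off-drug state ends |

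As printed, no row keeps its entry background. If a slip is assumed, only the first row is repaired. Interventions also conflicts with itself: if every treated patient's regimen is changed, the next sentence cannot treat alteration as something that happens in some cases.

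**3. Timing.** Baseline is before treatment. No section places the Madopar start or the change of regimen before baseline, and none sets a new stable period after it. A drug effect inside the change score is therefore possible, though not stated.

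**4. What that does to the comparison.** Let D_T and D_C be the mean drug-driven change in the QHN and sham arms.

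- Expected change within an arm = needling or sham effect + D for that arm. It cannot be read as a needling effect.
- Expected between-arm difference = needling effect + (D_T − D_C). One policy applied to both randomised arms gives D_T = D_C in expectation, and the drug term cancels.
- Variance rises only if the drug-driven change differs between patients, for example between those starting and those switching. The article gives nothing from which to size this.
- The term D_T − D_C departs from zero only if drug changes after randomisation differ by arm.

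**5. Size of that last term, on assumed inputs.** Bias = (difference between arms in the share with a motor-relevant drug change) × (mean shift per change). Neither input is in the article; the values below are assumptions.

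| Difference in share | Shift 3 points | Shift 8 points |
|---|---|---|
| 10% | 0.10 × 3 = 0.3 (7% of 4.11) | 0.10 × 8 = 0.8 (19%) |
| 20% | 0.20 × 3 = 0.6 (15%) | 0.20 × 8 = 1.6 (39%) |

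The direction is unknown.

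**The case against.** The strongest reply has four parts.

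- **One policy, randomised arms.** A common drug effect cancels in the contrast. This stands. A reader might infer that the primary comparison is confounded by Madopar; the text does not support that.
- **Item 5 governs status before entry.** A patient can be admitted off drugs and then started. This is fair as to sequence, but it leaves the stable-dose requirement with no evident function, and it does not touch the conflict inside Interventions.
- ***Changed* is probably a slip.** This is plausible, since the next sentence treats alteration as an exception. As step 2 shows, it repairs one row of three.
- **A condensed article may leave the timing to the full protocol.** This is true, so the absence of timing alone is no finding. The contradictory sentences are printed, however, and the timing belongs in their correction.

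Some further inferences are tempting but not supported:

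- **A quantified loss of power.** If a fraction f of patients gain g points from drug changes, SD = √(64 + f(1−f)g²). On the literal reading everyone starts or is changed, so f = 1 and the SD stays at 8.0. Unequal gains could raise it, but by an unknown amount, and whether 8.0 already reflects varied medication cannot be told from the article.
- **The control-arm figure of 0.25 as proof of an unchanged background.** It comes from a cited study that is not shown.
- **Unblinded prescribers.** The article says that acupuncturists could not be blinded. It does not say who prescribes. Efficacy assessors are described as blinded.
- **The adverse-event rule as a third contradiction.** Stopping a drug after a reaction is compatible with any background rule. It is only another route to drug changes after randomisation.

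**Conclusion.** The contradiction between Inclusion Criteria and Interventions holds on the printed text, and it survives the most charitable reading of *changed*. It concerns a co-treatment that acts on the primary outcome, so it needs correcting.

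The statistical consequence is limited. UPDRS-III change may include a drug effect, provided that drugs are started or changed after baseline. Within-arm change is then not interpretable as a needling effect, and variance may rise. The randomised difference is biased, as a measure of needling itself, only if later drug changes differ by arm. The article does not show that they would, but it does not exclude it: acupuncturists know the allocation, alterations are permitted, and drugs are halted for reactions. On the assumed inputs in step 5 this would amount to 7% to 39% of the planned difference. That range is an illustration, not an estimate for this trial.

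**What to change.** 1. **Reconcile Inclusion Criteria item 5 and Interventions** into one background-medication rule for both arms, covering patients off drugs, on Madopar and on other drugs, and stating when any start or change occurs relative to baseline. The clinical team must decide the rule; none is proposed here. The article mixes past and future tense, so the correction should also say what sites were actually instructed to do.
2. **Replace the unadjusted t-test on UPDRS-III change with an ANCOVA** adjusting for baseline UPDRS-III and medication status before randomisation (on or off anti-PD drugs). This can recover precision lost to differences between those two groups. It does not correct for drug changes after randomisation, which should not be entered as covariates.
3. **Tabulate by arm** the recorded drug doses at baseline, week 6 and week 14, and the drug changes, so that a reader can see whether they differ.
4. **Keep the comparison of all randomised patients as primary.**

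The cost is a wording amendment, one changed analysis sentence and one table. The article says that Madopar dosage and drug alterations are recorded, but not on which form. The sponsor should confirm that entry status and doses at the three assessments can be extracted. No change to the sample size follows from this point.

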### Treatment Group

The design of the treatment group was based on the theory of Traditional Chinese Medicine. In addition to the standard routine care, the treatment group received QHN therapy. The location and needling methods for acupoints are demonstrated in Table 1, Figure 2, which were located in four limbs, the neck, and the back. A tailored sterile, stainless-steel needle (length: 50 mm; diameter: 0.5 mm; QH; Chongqing, Figure 3) was inserted into the described acupoints at a depth of 25–40 mm. After the patients felt the *Deqi* sensation, the needles were removed and re-applied at a 30° angle. All needles were withdrawn with clean cotton balls pressed to the skin to prevent bleeding. Participants received a total of nine sessions of treatments within 6 weeks. Treatment was given 2 times per week for the first 3 weeks and 1 time per week for the following 3 weeks.

**Table 1 T1:** Location of acupoints in the treatment group.

**Session**	**Acupoints**	**Location**
1, 4, 7	EX-B2	0.5 *cun* lateral to the depression below the spinous process of the 4th cervical vertebra
	LI 10	on the dorsal-radial side of the forearm, 2 *cun* inferior the transverse crease of the elbow, on the line joining LI5 and LI11
	EX-UE	on the midpoint of the line between the top of anterior axillary folds and LI15 acupoint
	GB 29	at the lateral gluteal, the midpoint of the line between anterior superior iliac spine and the most convex point of the greater trochanter
	GB 33	on the lateral side of the knee, the depression above the external epicondyle of the femur
2, 5, 8	SJ14	in the depression posteroinferior to the acromion when arm is abducted
	LU5	on the transverse cubital crease, the radial side of the tendon of the biceps brachii
	SJ4	in the dorsal of the transverse crease of the wrist, the depression of the ulnar border of the total extensor tendon
	BL24	1.5 *cun* lateral to the depression below the spinous process of the 3th lumbar vertebra
	BL40	the midpoint of the transverse crease of the popliteal fossa
	BL58	on the lateral of the calf, 7 *cun* above the BL60 acupoint
3, 6, 9	LI14	7 *cun* above the transverse crease of the elbow, on the line joining LI11 and LI15
	PC3	on the transverse cubital crease, the depression of the ulnar border of the tendon of biceps brachii
	LI5	at the dorsal transverse crease of the wrist, at the depression between the tendons of the short extensor and long extensor of the thumb when the thumb is upward
	ST31	In anterior of the thigh, flush with the transverse crease of the hips, on the line joining the anterior superior iliac spine and the lateral side on the bottom of the patella
	LR8	on the medial side of transverse crease of the knee, the posterior edge of the medial condyle of the femur when bending the knee

^*^*Additional points could be chosen according to syndrome differentiation*.

*(1)constipation: ST25: (2) insomnia: BL14*.

**Figure 2 F2:**
[figure not shown]
Location of acupoints. **(A)** EX-B2; **(B)** LI10; **(C)** EX-UE & LI15; **(D)** GB29; **(E)** GB33; **(F)** SJ14; **(G)** LU5; **(H)** SJ4; **(I)** BL40; **(J)** BL58; **(K)** BL24; **(L)** LI14; **(M)** PC3; **(N)** LI5; **(O)** ST31; **(P)** LR8.

**Figure 3 F3:**
[figure not shown]
*Qihuang* Needle.

### Control Group

The control group of this study was provided sham-acupuncture therapy. Sham acupoints are defined as 20-mm lateral of the verum acupoints. To do so, a needle was inserted into the sham acupoints at a depth of 3 mm without any subsequent manipulation. At these points, the patient did not feel the *Deqi* sensation. Similar to the treatment group, sham treatment was given 2 times per week for the first 3 weeks and 1 time per week for the following 3 weeks.

### Outcome Measurements

All outcome measurements were taken at baseline (before treatment), 6 weeks after treatment, and 14 weeks after treatment.

### Primary Outcome Measurement

#### Parkinson's Disease Rating Scale-Part III Motor Examination (UPDRS-III)

Parkinson's Disease Rating Scale-Part III Motor Examination-III is an assessor-rated scale that is used to evaluate the motor function of patients with PD. It contains 18 items, and each item is scored “0–4” depending on the severity of the motor disability, in which “0” represents normal and “4” indicates severe impairment. Higher scores indicate severe motor function and disability. This scale effectively assesses the severity of PD and has demonstrated high efficiency, validity, and reliability (15).

### Secondary Outcome Measurement

#### Parkinson's Disease Daily Quality of Life-39 (PDQ-39

Parkinson's disease daily quality of life-39 is a questionnaire used to assess the health-related quality of life (HRQoL) of patients with PD (16). This questionnaire contains 39 questions and evaluates eight dimensions: mobility, activities of daily living, emotional wellbeing, stigmatization, social support, cognition, communication, and bodily discomfort. Each question has five choices, in which higher scores indicate higher incidence rates of the physiological or psychological status of the patients, suggesting a low HRQoL.

### Non-Motor Symptoms Scale for Parkinson's Disease (NMSS)

**Non-Motor Symptoms Scale for Parkinson's disease** is a 30-item scale for assessing the non-motor symptoms of PD. It is used to evaluate cardiovascular symptoms, sleep, cognition, memory, dysesthesia, gastrointestinal symptoms, and urinary symptoms. Each item is rated using a “1–3” and “1–4” scale, where the former represents the severity of the non-motor symptom, whereas the latter indicates its frequency. Higher scores indicate a more severe non-motor disorder. Validation of this tool has been shown by excellent correlations between the H-Y scale and UPDRS scores.

### Sample-Size Calculation

This trial used a clinical-superiority design to verify that QHN therapy's effect was superior to that of sham acupuncture. The primary outcome measure was the UPDRS-III score difference before and after the treatment. According to previous research (17), assuming the standard deviation (SD) to be 8.0 and the mean of the treatment effect of the two groups to be 4.36 and 0.25, respectively, the statistical power was 80%, and the significance level was 0.05. Using PASS software requires each group to contain no <61 patients. With an estimated 15% dropout rate, we planned to recruit 72 patients for each group, for a total of 144 patients.

### Statistical Analysis

We used mean and SD for normally distributed variables, or median (interquartile) for the variables not normally distributed, to summarize the participants' demographic, health conditions, and clinical outcomes at three different time points. Two statisticians, blinded to the group setting, analyzed the data independently *via* SPSS software (version 26.0). Missing data were imputed according to the last-observation-carried-forward (LOCF) principle. Furthermore, the data were analyzed by the intent-to-treat principle.

The normality of the variables was assessed using the normal probability plot. The continuous variables normally distributed were assessed by the student's t-test. Otherwise, the Mann-Whitney test or Wilcoxon test was applied. The Fisher's exact or the chi-square test was adopted for categorical data, and statistical significance was set at *p* < 0.05.

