**Methods:**

This trial is a multicenter, prospective randomized controlled clinical trial. We randomly allocated 144 participants to two groups of 72 patients. Patients in the treatment group were treated with QHN therapy. The control group had undergone insertion of acupuncture needles at sham acupoints not corresponded to acupuncture points. Participants in the verum treatment group and sham-acupuncture control group received 9 sessions over 6 weeks followed by 8 weeks of follow-up. The primary outcome was the change of motor function from baseline to weeks 6 and 14 measured by the PD Rating Scale-Part III Motor Examination (UPDRS-III). Secondary outcome measures included the change of PD daily quality of life-39 (PDQ-39) and Non-Motor Symptoms Scale for PD (NMSS) from baseline to weeks 6 and 14.

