## Background

Parkinson's disease (PD) is a progressive neurodegenerative condition in which patients present clinical motor symptoms, such as bradykinesia, rigidity, resting tremor of distal extremities, and postural instability (1). Additionally, patients with PD may develop a series of non-motor symptoms, such as depression, cognitive impairment, sleep disorder, and autonomic disturbance (2). Unfortunately, PD has become the second-most common neurodegenerative disorder that affects estimated 6 million people worldwide (3).

The core pathological changes of PD lie in intracellular inclusions containing aggregates of α-synuclein and striatal dopamine deficiency induced by the loss of neurons in the substantia nigra. With the discovery of the role of dopamine deficiency in PD, pharmacologic dopamine substitution treatment became the foundation of current drug therapies for PD (4). In addition to oral medications, surgical intervention, such as deep brain stimulation, has been beneficial to patients with troublesome motor fluctuations and dyskinesia due to the advanced stages of PD. However, there remain challenges in developing effective treatment options for PD with these advancements. Due to none of these treatments effectively modifies disease progression and/or delay disability, patients with PD can often suffer from progressive degeneration of motor function. As the benefits of medications wane over time with disease progression, effective management of tremor, gait, balance, posture, and dexterity are major challenges for therapeutics designed for PD movement disorders (5). Beyond these unmanaged motor symptoms, many non-motor symptoms add considerably to the overall burden of the disease (6).

Acupuncture has existed for over 4,000 years as one of the main treatments of traditional Chinese medicine. As an adjuvant therapy, acupuncture is widely used in the treatment of PD, particularly in East Asia (7). Numerous clinical trials have shown that acupuncture could improve motor symptoms and the quality of sleep, reduce the dose and frequency of anti-PD drugs, and alleviate their side effects (8–11). However, none of these studies could verify whether the benefits are due to the efficacy of the treatment or as a result of the placebo effect (12, 13).

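### LOCF, the stated missing-data method, gives early dropouts zero change and carries the end-of-treatment score into the week-14 primary visit, so the result can be biased in a direction not known beforehand

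*Protocol article*

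**What the plan says.** The Statistical Analysis section names one way of handling missing values: "Missing data were imputed according to the last-observation-carried-forward (LOCF) principle". It continues: "Furthermore, the data were analyzed by the intent-to-treat principle". The comparison is a two-group test: "The continuous variables normally distributed were assessed by the student's t-test", with a rank test if normality fails.

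The abstract's Methods paragraph defines the endpoint: "The primary outcome was the change of motor function from baseline to weeks 6 and 14". It also says that participants "received 9 sessions over 6 weeks followed by 8 weeks of follow-up". Outcome Measurements lists the assessments: "All outcome measurements were taken at baseline (before treatment), 6 weeks after treatment, and 14 weeks after treatment". Read with the abstract, these are baseline, the end of the six-week needling course, and eight weeks after it. No other outcome visit is listed.

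The Sample-Size Calculation allows for loss: "With an estimated 15% dropout rate".

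**The concern.** With three assessments, LOCF can do only two things.

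- **Loss before week 6.** The only score to carry is the baseline, so the change is set to zero at weeks 6 and 14.
- **Loss between weeks 6 and 14.** The score at the end of needling is used for a visit eight weeks after needling stopped.

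The second case matters most. Week 14 is part of the primary outcome, and its purpose is to show whether any benefit lasts. For every late dropout LOCF answers that question by assumption. If benefit fades, the week-14 difference is overstated. Early loss instead pulls the difference towards zero when the treatment works. The net direction depends on when patients leave, from which arm, and what would have happened to them, none of which is known when the analysis is fixed. Analysing as randomised does not help, because it fixes who is counted and not what value a missing patient receives.

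**Working it through.** **Inputs from the Sample-Size Calculation:** SD 8.0; mean changes 4.36 (QHN) and 0.25 (sham), difference 4.11; 80% power; significance level 0.05; 15% dropout; 72 per group.

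**Assumptions not in the article:** the timing of dropout, any imbalance between arms, the amount of fading by week 14, a correlation of 0.7 between week-6 and week-14 changes, and dropout unrelated to outcome.

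**1. The plan's own figure.** Normal approximation, two-sided: n = 2 × (1.960 + 0.842)² × 8² / 4.11² = 59.5, so 60. The exact t calculation gives 61 (power 79.7% at 60, 80.4% at 61). 61 / 0.85 = 71.8, so 72. The plan's 61 and 72 are reproduced. Expected loss is 0.15 × 72 = 10.8, about 11 patients per arm.

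**2. All 15% lost before week 6, both arms.** Each lost patient contributes zero:

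0.85 × 4.36 − 0.85 × 0.25 = 0.85 × 4.11 = 3.49, against a true 4.11.

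**3. True week-14 effect is zero (both arms at 0.25), some loss after week 6.** Late dropouts keep their week-6 score:

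| Assumed loss | Expected LOCF difference at week 14 | Simulated rejection at nominal 5% |
|---|---|---|
| 7.5% early and 7.5% late, both arms | 0.075 × 4.11 = 0.31 | about 5.6% |
| 15% late, both arms | 0.15 × 4.11 = 0.62 | about 7% |
| 20% late in QHN, 10% late in sham | (0.20 × 4.36 + 0.80 × 0.25) − 0.25 = 0.82 | about 9% |

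Changing the assumed correlation to 0.3 or 0.9 barely moves these figures.

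**4. Effect halves by week 14** (4.11 / 2 = 2.06), 15% late loss in both arms: 0.85 × 2.06 + 0.15 × 4.11 = 2.37 (2.36 before rounding the halved effect). Simulated rejection is about 42%, against about 30% for observed cases.

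**5. Standard error, 15% early loss.** The LOCF variance is 0.85 × 64 + 0.85 × 0.15 × mean²:

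- QHN: 54.4 + 0.1275 × 4.36² = 56.8
- Sham: 54.4 + 0.1275 × 0.25² = 54.4
- LOCF SE = √((56.8 + 54.4) / 72) = 1.24
- SE with 61 observed per arm = 8 × √(2/61) = 1.45

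The LOCF value is about 14% smaller (1.24 / 1.45 = 0.86). In simulation, however, the LOCF estimate itself varies with a standard deviation of about 1.24 to 1.26, which agrees with its model SE. The ratios nearly match: 3.49 / 1.24 = 2.81 and 4.11 / 1.45 = 2.83. Power is about 80% with either method, and with no true effect and equal early loss the type I error is about 5%.

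**The case against.** **Standard errors.** A reader might infer that LOCF makes standard errors and confidence intervals too small and so produces false significance. Step 5 does not support that. LOCF does count filled-in values as data, but its SE is right for the quantity it estimates. That quantity is a diluted effect, so the smaller SE and the smaller difference offset in the test. An interval that misses 4.11 does so through bias.

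**Progression.** The Background says "patients with PD can often suffer from progressive degeneration of motor function", which invites the argument that a frozen score is implausible. It carries little weight here. The article gives no rate of decline over 6 to 14 weeks, and its sample-size assumption for sham is a change of only 0.25. None of the figures above uses progression.

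**Dilution is conservative.** This stands. Zero is close to the assumed sham mean, and sham-based imputation of early QHN dropouts gives the same expected difference: 0.85 × 4.36 + 0.15 × 0.25 − 0.25 = 3.49. Early loss alone is therefore not a strong case against LOCF.

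**Corner cases.** This also largely stands. The 3.49 and the 0.62 each place all the dropout in one period, so they cannot both occur. The 0.82 needs an imbalance the article does not predict, and the Discussion suggests effects may be sustained rather than lost. Nor does unequal dropout by itself create a difference: when no one changes on average, carrying a score forward adds no bias.

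**Unseen analysis plan.** A separate analysis plan may add sensitivity analyses, so their absence here is no fault. LOCF is the only method stated, and the point rests on that statement.

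**Conclusion.** The point holds as a matter of bias. LOCF is a stated rule and not a detail left open. In this three-visit design it assigns zero change to early dropouts and assumes a lasting effect for late ones, at a visit that belongs to the primary outcome.

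The plausible size is modest. Early loss costs up to about 0.6 of the planned 4.11 points at 15% dropout. A fully faded effect would appear as a false benefit of roughly 0.3 to 0.8 points, with error rates of about 5.6% to 9%. The plan's means, SD and overall dropout rate are its own. The timing, imbalance, fading and correlation are assumptions, and the result moves with the first three.

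Confidence is high that LOCF suits the week-14 comparison badly. The article does not support a claim about the direction or size of bias in the eventual data. The change should be made, but the planned sample size does not fail because of this: about 61 observed per arm keep about 80% power at week 6.

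**What to change.** Replace LOCF as the primary method with a likelihood-based repeated-measures model on all observed UPDRS-III scores at weeks 6 and 14, adjusted for baseline, with the arm difference estimated at each visit. Multiple imputation is an acceptable alternative. Both are valid under missing at random. Add one sensitivity analysis for departures from that assumption, such as sham-based imputation. Keep LOCF as a supplementary analysis at most. Settle the wording before the data are unblinded.

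The cost is a change of analysis wording and a little more programming. SPSS 26, the package named in the article, fits the repeated-measures model, and no extra patients are needed for week 6. The downside is that missing at random cannot be tested. Patients with no post-baseline score add little to the model, so their outcome still rests on assumption, which is why the sensitivity analysis is needed.

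### The effect measure of the primary UPDRS-III analysis is not fixed: a normal probability plot with no stated criterion decides between a t-test and a rank test

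*Protocol article*

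**What the plan says.** The Statistical Analysis section of the Protocol article sets one rule for all continuous variables:

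- The check: "The normality of the variables was assessed using the normal probability plot".
- If the variable is judged normal: "The continuous variables normally distributed were assessed by the student's t-test".
- If not: "Otherwise, the Mann-Whitney test or Wilcoxon test was applied".
- The descriptive measure follows the same split: "We used mean and SD for normally distributed variables, or median (interquartile) for the variables not normally distributed".

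No separate analysis is named for the primary outcome, so the rule governs it. The Sample-Size Calculation section defines that outcome as a change score: "The primary outcome measure was the UPDRS-III score difference before and after the treatment". The Methods part of the Abstract places the change at two times, weeks 6 and 14. The trial is sized on means, "assuming the standard deviation (SD) to be 8.0 and the mean of the treatment effect of the two groups to be 4.36 and 0.25". Under Outcome Measurements, UPDRS-III is also recorded at baseline.

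**The concern.** The t-test addresses a difference in means. The Mann-Whitney test addresses whether values in one arm tend to exceed those in the other. When the two distributions differ in shape as well as location, these are different questions, and only the first yields points on the UPDRS-III scale to set against the 4.11 points used for planning. Under the stated rule, nobody can say before the data are seen which question the trial will answer.

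Three features add to this:

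- A plot reading without a criterion is a judgement, so two competent readers of the same plot could choose differently.
- The rule works variable by variable. Week 6 could be reported as a mean difference and week 14 as a rank test with medians.
- The fallback names two tests without saying which applies where. Wilcoxon may mean the rank-sum test, which is equivalent to Mann-Whitney, or the signed-rank test, which is a paired comparison.

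Separately from the switch, neither named test uses the baseline UPDRS-III score as a covariate, although it is collected.

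**Working it through.** **1. Which branch does the sample size belong to?** Inputs from the Sample-Size Calculation section: means 4.36 and 0.25, SD 8.0, power 80%, significance level 0.05, dropout 15%. Sidedness is not stated.

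- Difference: 4.36 − 0.25 = 4.11.
- Normal approximation, two-sided: n = 2(1.960 + 0.842)² × 8.0² / 4.11² ≈ 59.5, so 60 per group.
- Noncentral t, two-sided: 60.45, so 61 per group, as stated (power at 61: 80.4%). A one-sided 0.05 test gives 47.5, so 48, which does not match.
- Dropout: 61 / 0.85 = 71.8, so 72 per group, as stated.

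The plan's figures reproduce exactly for a two-sided, two-sample t-test. If the rank test were the fixed analysis and the data were normal (asymptotic relative efficiency 0.955), the numbers would be 61 / 0.955 = 63.9, so 64 evaluable, and 64 / 0.85 = 75.3, so 76 recruited. Only the t-test branch matches the design.

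**2. Does the rule inflate type I error, and how often does the choice matter?** Simulation: 61 per group, 8,000 trials per setting, effect 0 or 4.11/8.0 = 0.51 SD as a pure shift. The plot reading is replaced by a Shapiro-Wilk test on pooled residuals, with the rank test used if p ≤ 0.05. This stand-in and the four distributions are assumptions, because the article gives no distribution for UPDRS-III change.

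| Distribution | Type I error, rule applied | Power, t-test | Power, rule applied | Verdicts differ at planned effect |
|---|---|---|---|---|
| Normal | 4.8% | 80.2% | 80.3% | 5.4% |
| Gamma, skewness 1 | 5.2% | 80.8% | 85.9% | 7.6% |
| t, 5 df | 5.1% | 81.2% | 87.5% | 9.7% |
| Exponential | 4.8% | 79.7% | 97.5% | 17.8% |

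With a Shapiro-Wilk cut-off of 0.01 instead, the type I error of the rule was 4.7%, 5.3%, 5.2% and 4.8%. The Monte Carlo standard error near 5% is √(0.05 × 0.95 / 8000) = 0.24 percentage points, so all these values are compatible with 5%.

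The last column compares both tests on the same data. It shows how often the choice of test decides significance, not how often the plan's rule errs.

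**3. How much does the choice depend on how strictly the plot is read?** Take cut-offs of 0.01 and 0.10 as assumed lenient and strict readings. At the planned effect they select different tests in 8.6% of trials (normal), 6.6% (skewness 1), 22.3% (t, 5 df) and 0% (exponential). The choice is least stable for moderate departures from normality.

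**The case against.** **The error rate is held.** A reader might infer that a data-dependent choice of test breaks the 5% level. The simulation does not support that. Reporting the smaller of the two p-values would give 5.5% to 7.1%, but the plan selects by distribution shape, not by p-value. The analysts are blinded to group, and the Blinding section says that the analyst was hired separately and had no part in design or clinical work. This objection stands in full. Blinding does not, however, supply a plot criterion or fix the effect measure.

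**The switch has a purpose.** It would be wrong to say that it gains nothing. On the non-normal shifts tried, it raised power over the t-test by about 5 to 18 percentage points. This stands. The argument for a fixed mean-based analysis is the effect measure, not power.

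**The two analysts.** The article says that "Two statisticians, blinded to the group setting, analyzed the data independently". A reader might infer that each could reach a different primary test with no rule to settle it. The text does not say that each analyst chooses a test. Independent double analysis is ordinarily a check, and its reconciliation procedure is a detail that an article leaves to the fuller document.

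**Variables versus residuals.** A reader might also object that normality is assessed on variables rather than residuals. For a two-group comparison, normality within each arm is the residual assumption, and the article does not say that the arms are pooled.

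**Baseline adjustment.** The switch does not cause its absence. A fixed t-test on change scores would not adjust either.

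**The analysis plan may settle it.** It may, but the article does not leave the matter open. It states a complete rule, and a later plan would have to depart from that rule.

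**Conclusion.** The point holds as one about an undetermined effect measure. The stated rule leaves the primary hypothesis and its scale to a judgement on the trial data, allows them to differ between the two primary time points, and in one branch yields no estimate comparable with the 4.11-point planning difference.

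Its size is moderate. The choice of test would change the significance verdict in roughly 5% of trials at the planned effect if the data are normal, and in about 8% to 18% under the skewed and heavy-tailed distributions tried. Those figures rest on assumed distributions, a pure location shift and 61 per group. The type I error result also rests on Shapiro-Wilk as a stand-in for the plot. That the effect measure is not fixed rests on the text alone.

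**What to change.** State one primary analysis that applies whatever the plot shows: the between-group mean difference in UPDRS-III with 95% CI, from ANCOVA adjusted for baseline UPDRS-III, in the same form at weeks 6 and 14. Use residual plots for description only. Keep Mann-Whitney as a named supportive sensitivity analysis, and have the second statistician replicate the fixed analysis.

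The cost is wording. Baseline scores are already collected, trial conduct does not change, and the stated 61 evaluable and 72 recruited per group stand because they were derived for a mean difference. The downside is power: if change scores are strongly non-normal, the mean-based test may be less powerful than the rank test (79.7% against 97.5% in the exponential setting, the most extreme one tried).
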